### Intervention

The intervention was based on a pilot study with 13 patients, performed from November 2009 to January 2010, to test feasibility of SMS-IVR. The mean response rate was 62%. A significant reduction of highest pain intensity was found between pre- and post-test (p = 0.018). Pain fluctuated more in patients included in this pilot study than would be expected in patients who will be included in the present study, because only patients in palliative care were included in the pilot study.

Next, we developed a multifaceted intervention with hospital as cluster. Multifaceted interventions are proven to be more effective than single interventions [66,67]. Oncologists and nurses in the hospitals allocated to the intervention condition will be trained in-person, and GPs of patients that take part in the study will be offered a web-based training on the most important aspects of the CPG. Patients in the intervention condition will get SMS-IVR and will receive a personal advice by phone how to reduce their pain if their pain rating is 5 or higher on a NRS of 0 (no pain at all) to 10 (worst pain you can imagine). The research nurse of the hospital, specialised in pain treatment and trained for this project, will provide the personal advice.

The training for oncologists and nurses consists of three one-hour sessions, all given in-person; one main session at baseline, session two at six months, and the final session at 12 months. The first session will include the aim of the study, the main aspects of pain treatment in patients with cancer, pain measurement, and an instruction of the SMS-IVR system in detail. The next two sessions aim to summarise the first session and discuss problems associated with the implementation of the guideline.

Figure 3 shows the workflow of the SMS-IVR intervention. Patients receive SMS-IVR minimal once a week (Tuesdays), twice a day, during 12 weeks (Figure 2). SMS alerts are used as a reminder that they will receive an automatic telephone call 15 minutes later with IVR. SMS alerts will be received at 09:45 a.m. and at 2:45 p.m. At 10 a.m. and at 3 p.m. the patients will be called and invited to rate their pain on a scale of 0 (no pain) to 10 (worst pain imaginable). Morning: Rate your pain by choosing a number that best describes your WORST pain in the last 24 hours. Afternoon: Rate your pain at this moment.

**Figure 3 F3:**
[figure not shown]
**Workflow SMS alerts**. Figure 3 shows the workflow of the SMS-IVR intervention. Patients receive SMS-IVR minimal once a week (Tuesdays), twice a day, during 12 weeks. SMS alerts are used as a reminder that they will receive an automatic telephone call 15 minutes later with IVR. SMS alerts will be received at 09.45 a.m. and at 2.45 p.m. At 10.00 a.m. and at 3.00 p.m. the patients will be called and invited to rate their pain on a scale of 0 (no pain) to 10(worst pain imaginable). If the highest pain score is 5 or more, the research nurse will contact the patient. If a patient has five or higher on an NRS on Tuesday he/she will again receive two SMS alerts the next day (Wednesday); the procedure will be repeated. For those who still have a pain score of five or higher on Wednesday, the procedure will be repeated again at Thursday. The whole procedure of the SMS-IVR system described in figure 1 will start again the next week at Tuesday.

If the highest pain score is 5 or more, the research nurse will contact the patient and will ask: 'at what time/period the patients experienced the worst pain and whether the pain limited daily activities?'

Any patient who has 5 or higher on an NRS on Tuesday will again receive two SMS alerts the next day (Wednesday); the procedure will be repeated. For those who still have a pain score of 5 or higher on Wednesday, the procedure will be repeated again at Thursday.

The whole procedure of the SMS-IVR system described in Figure 3 will start again the next week at Tuesday. For the days without SMS, patients will follow the instructions of the research nurse for those days: increase doses with ... when pain is still 5 or higher; keep doses stable at ... when pain is below 5. Thus, at the first day patients will be phoned, because pain score was 5 or higher, the pain treatment protocol will be chosen for the whole week. However, this protocol may be changed by the research nurse when pain intensity remains 5 or higher.

In addition, both patients in the intervention and the control condition will fill in a pain diary on Tuesdays for 12 weeks. They will do this twice each Tuesday, once between 8:00 and 12:00 a.m., and once between 12:00 a.m. and 17:00 p.m.. However, there should be a minimum of five hours between the morning and afternoon measurement. The pain diary reports pain intensity with NRS, use of pain medication, and any side effects of the medication. Patients will also receive a leaflet on cancer pain of the Dutch Cancer Society. In addition, oncologists and nurses will receive a leaflet for professionals on pain treatment of the VIKC.

### Control

Patients in the control condition will also receive a leaflet on cancer pain. These patients will also complete a pain diary on Tuesdays during the 12-week period in the same way as the patients in the intervention condition. In addition, professionals will be offered a leaflet on pain treatment as a summary of the pain management guideline will be offered to GPs in the control condition. This is done to study the effect of the 'active' implementation (interactive web-based training), with the 'inactive' control condition (offering the most important aspects of the guideline as a tool to use in practice).

### Primary and secondary outcome and measurement instruments

The primary outcomes of this implementation study include:

The first primary outcome is the percentage of all patients that visit the medical oncology outpatient clinic with adequate pain therapy/medication. Pain treatment adequacy will be calculated with both the Cleeland's Pain Management Index (PMI)[68] and Ward's variation of the PMI [33]. It is the most used measure for adequate pain treatment [33]. Cleeland's PMI compares the most potent analgesic prescribed, with patient's reported worst pain level on the Brief Pain Inventory (BPI). In addition, Ward's variation of the PMI compares the most potent analgesic used by a patient used with that patient's reported worst level of pain on the BPI. The worst score on the BPI will be determined (1 to 3, mild pain; 5 to 6, moderate pain; and 7 to 10, severe pain), where the absence of pain will be defined as 0, mild pain as 1, moderate pain as 2 and severe pain as 3. The worst score on the BPI is used because it is often used clinically as an indicator for treatment [69]. PMIs will be computed by subtracting the pain level from the analgesic level, ranging from -3 (a patient with severe pain receiving or using no analgesic drug) to +3 (a patient with no pain receiving or using a strong opioid or equivalent). PMI-scores of 0 or higher are considered to be a reflection of adequate pain treatment, whereas negative PMI-scores are considered to reflect inadequate pain treatment.

The second primary outcome is the mean pain intensity of cancer patients, measured with an NRS (SMS alerts and pain diary). The NRS is the most appropriate choice to use in practice for pain intensity [70,71] (see Table 1). The pain dairy is used to obtain additional information (medication use, side effects of medication) and to report pain intensity in the control group.

**Table 1 T1:** Validated patient questionnaires/scales used in this study

Measurement	Validated questionnaires	Time points (M = month)
**Pain intensity**	A. Numeric Rating Scale (NRS) B. Brief Pain Inventory Short form (BP-SF)	A. M0-M3/M9/M15 B. M0/M3/M9/M15

**Multidimensional aspects of pain**	McGill pain questionnaire (MPQ)	M0/M3/M9/M15

**Pain interference with function**	Brief Pain Inventory Short form (BP-SF)	M0/M3/M9/M15

**Adequate pain treatment**	Ward's Pain Management Index (PMI-revised)	M0/M3/M9/M15

**Quality of life**	European Organization for Research and Treatment of cancer Quality of Life Questionnaire- C30 (EORTC QLQC30)	M0/M3/M9/M15

**Neuropathic pain**	Neuropathic Pain Diagnostic Questionnaire (DN4-SF) (first two questions)	M0/M3/M9/M15

**Problems in daily life associated with cancer**	Distress Thermometer (DT)	M0/M3/M9/M15

**Emotions related to cancer**	Hospital Anxiety and Depression Scale (HADS)	M0/M3/M9/M15

**Performance status**	Karnofsky Performance Scale (KPS)	M0/M3

**Self-efficacy for communication about pain with oncologist**	Perceived Efficacy in Patient-Physician Interactions (PEPPI-5)	M0/M3

The secondary outcomes of this study include:

1. Percentage of medical records in which pain of new patients in the outpatient oncology clinic is registered with a validated instrument, such as the NRS or visual analogical scale (VAS). These data will be collected retrospectively via medical records.

2. Quality of life of patients with The European Organization for Research and Treatment of Cancer Core Quality of Life Questionnaire Quality of life (EORTC QLQ-C30) questionnaire [72]. EORTCQLQ-C30 will be used to measure quality of life [72].

3. Knowledge of medical oncologists and nurses of the content of the guideline with a self-developed and pilot-tested knowledge questionnaire and vignette study. This knowledge questionnaire and vignette study are based on the recommendations in the guideline, with input from specialists in pain treatment and GPs.

4. Pain intensity and impact of pain on daily activities will be measured with the Brief Pain Inventory Short Form (BPI-SF) [73]. This questionnaire consists of four questions whereby pain intensity is rated on an 11-point numerical scale (NRS) raging from 0 (no pain) to 10 (worst pain ever).

5. Insight in the multidimensional aspects of pain with the Short-form McGill Pain Questionnaire [74]. To measure sensory, affective, and evaluative qualities of pain the McGill Pain Questionnaire Dutch version (MPQ-DV) will be used [75].

6. Performance status of patients will be measured with the Karnofsky scale [76]. It is based on the assessment by the oncologist of the patient's ability to perform usual daily activities.

7. We will identify neuropathic pain by using the two first questions of the Douleur Neuropathic 4 questions questionnaire, short form (DN4-SF) [77].

8. To assess multidimensional problems (work, family, *et al*.) related to cancer the distress thermometer (DT) will be used [78].

9. Prevalence of anxiety and depression will be measured with the Hospital Anxiety Depression Scale HADS [79].

10. Patients' experiences with the SMS-IVR system will be assessed with semi-structured interviews.

11. Self-efficacy for communicating about pain with oncologists will be assessed with the mean response to the five items in the Perceived Efficacy in Patient-Physician Interactions scale (PEPPI-5), with the wording of the items modified to refer to communication about pain with oncologists [80] (Table 1).

### Sample size

Sample size calculations of the present study with three clusters of two hospitals, are based on the expected effect of the intervention on the PMI. However, the present study is the first investigating the effects of using an SMS-IVR system in cancer pain management. Several studies show that adequate pain relief can be achieved in 70 to 90% of patients with cancer [44-47]. To achieve this, the present study aims to find out whether our implementation strategy reduces the negative PMI from 42% [6] to 20% [44-47] of all cancer patients visiting the outpatient clinic.

To detect a difference with 80% power (alpha = 0.015), we need 90 patients per condition. Accounting for clustering resulted in an intraclass correlation coefficient (ICC) of 0.015. Based on the ICC and three hospitals per condition, we need 30 patients per hospital. Taking into account a dropout rate of 15%, we need 35 patients per hospital, for a total of 210 patients.

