**Figure 1 F1:**
[figure not shown]
**Flowchart cluster randomisation of clinics**. Figure 1 shows the cluster randomisation of clinics. A cluster RCT with two arms will be performed in six oncology outpatient clinics of hospitals, with three hospitals in the intervention and three in the control condition. Clusters of hospitals will be determined based on number of beds and number of medical oncologists. We require 35 patients per hospital, a total of 210 patients.

1. Training of oncologists and nurses involved in cancer care on the most important aspect of the CPG comprising of three one-hour sessions, one main session at baseline, session two at month six, and the final session at month twelve (intervention arm).

2. Patients will receive SMS-IVR and personal advice by phone on how to reduce their pain if their pain rating is 5 or higher on a numeric rating scale (NRS) of 0 (no pain at all) to 10 (worst pain you can imagine) (intervention arm).

3. Patients will receive a leaflet on cancer pain of the Dutch Cancer Society (in both arms).

4. Oncologists and nurses will receive a leaflet for professionals on pain treatment of the Comprehensive Cancer Centre organisation (VIKC) (both arms).

5. GPs in the Netherlands will be offered a web-based training on the most important aspects of the CPG (intervention arm).

Follow-up measurements in all hospitals will be conducted to study the long-term effect of the intervention. Regarding the patients recruited in this study, the intention to treat principle will be used (Figure 2).

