In addition, our study will show possible barriers in SMS-IVR use for pain reporting in patients with cancer. This has never been done before. One of the possible barriers accounted for in the present study is asking too often about cancer pain and this could be experienced as confrontation with their disease. However, nothing is known yet about a proper frequency to ask patients about their pain. In the present study, patients will receive a weekly SMS alert twice a day. In the pilot study, patients received SMS alerts four times a week for four weeks. To achieve a similar response rate and compliance as was achieved in the pilot study, the frequency of SMS alerts has been reduced in the present study. It has been reduced to once a week if there is no pain and to maximal three times a week if pain remains present because the intervention period is three times as long. Asking patients about pain improves insight in pain intensity of professionals and it increases registration of pain [83,84]. Asking about pain in itself can reduce pain intensity [84]. Therefore, using SMS-IVR as a way to systematically measure pain is expected to reduce pain intensity.

Apart from the SMS-IVR, a pain dairy is necessary to obtain data on pain intensity in the control group and additional information in both control and intervention group. Asking about pain by measuring pain intensity with a pain diary in itself can reduce pain intensity [84]. Therefore, we expect that pain intensity difference between the intervention and the control group will be smaller. However, the possibility of earlier treatment is restricted to the intervention group. We expect an increase in motivation of patients to take part in the control condition and higher compliance during the study than without the pain dairy. However, because patients are expected to be more motivated to participate when SMS alerts are offered to them, this may cause selection bias. However, it was not possible to randomise at patient level, because of the multifaceted intervention. Oncologists and nurses should be trained before inclusion of patients.

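### The 90 patients per condition behind the stated 80% power match the individually randomised requirement and do not change after the ICC step; with the plan's own ICC, power at the printed alpha is about 59–62%

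*Protocol article*

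**What the plan says.** The Sample size section bases the trial on the proportion with a negative Pain Management Index (PMI). The aim is to find out whether the strategy "reduces the negative PMI from 42% [6] to 20% [44-47] of all cancer patients visiting the outpatient clinic". It continues: "To detect a difference with 80% power (alpha = 0.015), we need 90 patients per condition". The clustering step follows: "Accounting for clustering resulted in an intraclass correlation coefficient (ICC) of 0.015", and then "Based on the ICC and three hospitals per condition, we need 30 patients per hospital". The last step is dropout: "Taking into account a dropout rate of 15%, we need 35 patients per hospital, for a total of 210 patients". The legend to Figure 1 confirms six clusters, "with three hospitals in the intervention and three in the control condition". The Study design section says that hospitals are randomised within three matched pairs. The section does not say whether alpha is one-sided or two-sided, and it prints no design effect.

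**The concern.** Three hospitals of 30 make 90, which is the number given before clustering was mentioned. An adjustment for a positive ICC should have raised it. The only later increase, from 30 to 35 per hospital, is attributed to dropout.

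The wording also presents the ICC as an output of the calculation, when it has to be an assumed input. Its value is the same as the unusual alpha, so one of the two may have been copied from the other.

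Adequate pain treatment by PMI is the first primary outcome, and the whole sample size rests on it. If clustering was left out, the trial relies on a power that its own inputs do not give. If alpha is the misprint, the published significance level of the primary test is wrong.

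**Working it through.** **Inputs, all from the Sample size section:** p1 = 0.42, p2 = 0.20, power 80%, alpha 0.015, ICC 0.015, three hospitals per condition, 30 patients per hospital (35 before dropout). Two-sided testing is my assumption.

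**1. Reproduce the 90 without clustering.**
- z(0.9925) = 2.432 and z(0.80) = 0.842; their sum squared is 10.72.
- Unpooled: n = (0.42 × 0.58 + 0.20 × 0.80) × 10.72 / 0.22² = 0.4036 × 10.72 / 0.0484 = 89.4, rounded up to 90.
- Pooled variance under the null (mean rate 0.31): n = (2.432 × √0.4278 + 0.842 × √0.4036)² / 0.0484 = 93.4.

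The unpooled formula gives the printed figure exactly, with no inflation.

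**2. Check the clustering step.** 30 per hospital × 3 hospitals = 90, so the figure is the same before and after the ICC is introduced. The move to 35 is the dropout allowance (35 × 0.85 = 29.75, about 30 analysed).

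**3. Apply the plan's own ICC.**
- Design effect = 1 + (30 − 1) × 0.015 = 1.435.
- Effective size = 90 / 1.435 = 62.7 per arm.
- Standard error = √(0.4036 / 62.7) = 0.0802, so 0.22 / 0.0802 = 2.742.
- Unpooled power at two-sided 0.015: Φ(2.742 − 2.432) = Φ(0.310) = 62%. Pooled: 59%.

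**4. Suppose nobody drops out.** With 35 per hospital the design effect is 1 + 34 × 0.015 = 1.51, and the effective size is 105 / 1.51 = 69.5 per arm.

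**5. Repeat with alpha 0.05, in case 0.015 is a misprint.** The normal-approximation results are:

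| Two-sided alpha | 90 per arm analysed | 105 per arm analysed |
|---|---|---|
| 0.015 (as printed) | 59–62% | 65–68% |
| 0.05 (possible misprint) | 77–78% | 81–82% |

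**6. Few clusters (illustration only).** Normal quantiles flatter a comparison of three hospitals with three. With the same noncentrality (2.742), an unpaired cluster-level t-test on 4 degrees of freedom has about 27% power at alpha 0.015 and 55% at alpha 0.05, ignoring any gain from pairing.

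**The case against.** The strongest reply is that the text says the ICC was used, so its omission is an inference. If alpha is the misprint, 90 could already include clustering. One-sided 0.05 with a continuity correction needs 63 per arm, and 63 × 1.435 = 90.4. This stands as a possibility, and for that reason the point is worded as what appears to have happened. It is still the weaker reading: it replaces the printed alpha and adds a one-sided test and a correction that the section does not mention. The printed inputs need only the standard two-sided formula.

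It also stands that the shortfall depends on alpha. At two-sided 0.05 it is two or three percentage points, and it disappears by normal approximation if all 105 per arm are analysed, which the intention-to-treat statement under Study design makes a reasonable case to consider. At the printed alpha a shortfall remains either way.

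A reader might draw three stronger conclusions that the documents do not support:

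- **That 27% or 55% is the trial's power.** These figures assume an unpaired hospital-level test. The Statistical analysis section names repeated-measures GLM ANOVA, and hospitals are randomised in pairs. A paired hospital-level analysis would have 2 degrees of freedom and an unknown gain from matching. The figures show only the direction of the penalty.
- **That the right sample size is 90 × 1.435.** That product holds hospitals at 30 patients each. With three hospitals per arm fixed, more patients mean larger clusters and a larger design effect, so simple multiplication understates the requirement.
- **That the 42% control rate is too high because controls keep a diary.** The Discussion says "Therefore, we expect that pain intensity difference between the intervention and the control group will be smaller", but this concerns pain intensity. PMI also depends on the analgesic level, and nothing in the article says that the diary lowers the rate of negative PMI.

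**Conclusion.** The point holds as a contradiction between printed figures. It is not a complaint about missing detail: the article prints alpha, power, both rates, the ICC, the number of hospitals and the result, and these do not agree. Taken as printed and two-sided, 90 per condition gives about 59–62% power, not 80%, and 65–68% with no dropout at all. Both ranges precede any penalty for having only six hospitals in three pairs.

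The result rests on a two-sided test, the stated ICC, equal hospital sizes and a normal approximation, with no credit for pairing or baseline measurements. If alpha was meant to be 0.05 two-sided, the normal-approximation power is close to 80%, and the error lies mainly in the printed alpha. Either the stated power or the stated alpha must be corrected; the article alone does not show which.

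**What to change.** Keep the 210 patients and rewrite the sample-size paragraph so that it:

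1. confirms the alpha of the primary test and whether it is one-sided or two-sided;
2. presents the ICC of 0.015 as an assumed input;
3. shows the design effect (1.435 at 30 per hospital);
4. restates the power, or the detectable difference, that 30 analysed patients in each of three hospitals per arm deliver, using the degrees of freedom of the planned analysis, and says that few clusters lower it further.

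The 4-degree-of-freedom figures may serve as an illustration if their assumptions are stated, but not as the trial's power. The cost is one corrected paragraph and probably a less favourable stated power. No extra patients and no change to trial procedures are needed. The change does not restore the power; it makes the stated figure true.

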**Methods/design:**

A cluster randomised controlled trial with two arms will be performed in six oncology outpatient clinics of hospitals in the Southeastern region of the Netherlands, with three hospitals in the intervention and three in the control condition. Follow-up measurements will be conducted in all hospitals to study the long-term effect of the intervention. The intervention includes training of professionals (medical oncologists, nurses, and general practitioners) and SMS-IVR to report pain in patients with cancer to improve pain reporting by patients, pain management by medical oncologists, nurses, and general practitioners, and decrease pain intensity.

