### Statistical analysis

To measure the effect of the implementation the PMI and NRS will be used and tested with general linear model analysis of variances (GLM ANOVA) repeated measures. Qualitative content analysis will be used to analyse the results of the focus group discussions and to analyse the interviews to evaluate the SMS alert intervention. Qualitative analysis will be supported by the use of the Atlas.ti software programme.

Data collected via SMS-IVR will be analysed for descriptive data: how did pain scores change and fluctuate in the whole period, what actions were taken by the research nurse, and did this intervention help the patients to manage pain? Subgroup analysis will be conducted. Differences in subgroups of the effectiveness of the intervention are expected. Subgroups will be classified by: age, gender, race, education, performance status, and classification of malignant tumors (TNM stage). The most recent version of SPSS will be used to perform the statistical analysis.

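### The sample-size section prints 0.015 both as alpha and as ICC, and its figures cannot all hold: once clustering is counted, 90 per condition gives at most about 62% power at alpha 0.015, not 80%

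*Protocol article*

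**What the plan says.** All the planning figures are in the Sample size section of the protocol article.

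- **Target effect:** the strategy is to be tested on whether it "reduces the negative PMI from 42% [6] to 20% [44-47] of all cancer patients visiting the outpatient clinic".
- **Alpha, power and number:** "To detect a difference with 80% power (alpha = 0.015), we need 90 patients per condition".
- **Clustering:** "Accounting for clustering resulted in an intraclass correlation coefficient (ICC) of 0.015".
- **Per hospital:** "Based on the ICC and three hospitals per condition, we need 30 patients per hospital".
- **Enrolment:** "Taking into account a dropout rate of 15%, we need 35 patients per hospital, for a total of 210 patients".

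The Statistical analysis section says that "the PMI and NRS will be used and tested with general linear model analysis of variances (GLM ANOVA) repeated measures" and names no significance level. No other alpha for this trial appears in the article, and nowhere is the test said to be one-sided or two-sided.

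**The concern.** Two features of the section raise doubt.

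First, two unrelated quantities carry the same figure in adjacent sentences. As an alpha, 0.015 is not a customary level. It also does not match an equal split of 5% over the primary outcomes: 0.05 / 2 = 0.025 for the two listed, or 0.05 / 3 = 0.0167 if the two PMI versions and the NRS are counted separately. The sentence on clustering is muddled too, because it presents the ICC as a result of allowing for clustering when it is an input.

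Second, the number does not move when clustering is brought in. The section asks for 90 per condition, then invokes the ICC, then asks for 30 in each of three hospitals, and 3 x 30 is again 90. Either 90 is the number before clustering, and nothing was added, or it is the number after clustering, and the steps leading to it are not shown.

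The stated 80% power depends on which of these is true, and the alpha is also the level that a positive claim must meet. If 0.015 is a misprint and is corrected only after the results are known, the correction could look chosen to suit them.

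**Working it through.** **Inputs.** From the Sample size section: p1 = 0.42, p2 = 0.20, power 80%, alpha 0.015, ICC 0.015, 30 patients in each of three hospitals per condition. The two-sided test and the unpooled normal approximation are my assumptions. The alternative alpha of 0.05 is also mine; the article does not print it.

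**1. Reproduce the printed 90.** The formula is n = [p1(1 - p1) + p2(1 - p2)] x (z_alpha + z_power)² / (p1 - p2)².
- Variance term: 0.42 x 0.58 + 0.20 x 0.80 = 0.4036.
- Squared difference: 0.22² = 0.0484.
- Alpha 0.015: z = 2.432 + 0.842 = 3.274, so n = 0.4036 x 3.274² / 0.0484 = 89.4, rounded up to 90.

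The printed figure is reproduced, with no allowance for clustering.

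**2. Add the stated clustering.** Design effect = 1 + (30 - 1) x 0.015 = 1.435.
- Alpha 0.015: 89.4 x 1.435 = 128 per condition.
- Alpha 0.05: z = 1.960 + 0.842 = 2.802, so n = 65.5 before clustering, and 65.5 x 1.435 = 94 after.

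With three hospitals fixed, a larger sample means larger clusters and a larger design effect. Solving n = r x [1 + (n/3 - 1) x 0.015], where r is the unclustered number, gives n = 0.985r / (1 - 0.005r). That is 159 per condition at 0.015 and 96 at 0.05, so 128 and 94 are the lower figures.

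**3. Power at 90 per condition.** The effective number is 90 / 1.435 = 62.7.
- Without clustering: standard error = √(0.4036 / 90) = 0.0670, and 0.22 / 0.0670 = 3.285.
- With clustering: standard error = √(0.4036 / 62.7) = 0.0802, and 0.22 / 0.0802 = 2.742.
- Power = Φ(ratio - z_alpha). For example, with clustering at alpha 0.015, Φ(2.742 - 2.432) = Φ(0.310) = 62.2%.

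| Two-sided alpha | No clustering | Design effect 1.435 | Cluster-level t test, 4 df |
|---|---|---|---|
| 0.015 | 80.3% | 62.2% | 27% |
| 0.05 | 90.7% | 78.3% | 55% |

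The last column uses the same clustered standard error but refers the result to a t distribution with 6 - 2 = 4 degrees of freedom (critical values 4.088 and 2.776, noncentrality 2.742).

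**4. Sensitivity to the formula.** With the pooled variance, power with clustering is 59% at 0.015 and 77% at 0.05, and the clustered numbers are 135 and 99 per condition. At alpha 0.05 with clustering, the only variant tried that comes out close to 90 is one-sided with a continuity correction: 63 x 1.435 = 90.4. The article mentions neither feature.

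**5. Weight of the threshold.** If the planned effect is real, the chance that p lies between 0.015 and 0.05 is 90.7% - 80.3% = about 10% without clustering, and 78.3% - 62.2% = about 16% with it.

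**The case against.** The best defence is that the article prints one alpha and that 90 follows from it. Alpha 0.015, 80% power and 42% against 20% give 89.4, which rounds up to 90. A printed alpha that regenerates the printed number is evidence against a slip, and nothing makes an alpha of 0.015 wrong in itself. A condensed article may also leave the reason for the alpha, and the level used at analysis, to the full protocol or analysis plan. This stands: the silence of the Statistical analysis section is not by itself a fault.

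A reader might infer that the ICC was copied into the place of the alpha and that 0.05 was meant. The documents do not show this. Two-sided 0.05 with clustering needs 94 to 99 per condition, or 32 per hospital when solved with three hospitals fixed, rather than the printed 90 and 30. It is a near fit, while 0.015 without clustering is an exact one.

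A reader might also infer that the 80% holds under one of the two alphas and fails under the other. That is not so either. With clustering counted, neither alpha reaches 80% at 90 per condition.

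The defence does not remove the conflict. The exact fit exists only without a design effect, and the section says clustering was accounted for. It is also true that the power loss comes from the design effect rather than from the duplicated figure. But adding a design effect to the text would still leave open which alpha it belongs with, so the two have to be settled together.

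**Conclusion.** The point holds in this form: the printed alpha, ICC, cluster size and number per condition do not jointly give the stated 80% power. At two-sided 0.015 the shortfall is about 18 percentage points (80% to 62%), and about 128 per condition would be needed. If 0.05 was meant, the shortfall is about 2 points (78%), and 94 would be needed. A misprinted alpha is possible but not proven.

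These results assume a two-sided test, the stated ICC, equal hospitals of 30 and a single comparison of proportions. The 62% and 78% are upper figures, because the normal approximation is generous with three hospitals per condition; a cluster-level t test gives about 27% and 55%. The planned repeated-measures analysis could have a different power, but the section bases its calculation on the PMI percentages.

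**What to change.** Before any comparison of the arms:

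1. In the Sample size and Statistical analysis sections, confirm one alpha and its sidedness for the primary outcomes. If 0.015 is intended, give its reason; if it is a misprint, correct it.
2. Show the calculation in order: number before clustering, design effect 1 + (30 - 1) x 0.015 = 1.435, number after clustering.
3. Restate the power at 90 per condition with clustering: at most about 62% at 0.015 or about 78% at 0.05 (two-sided normal approximation), together with the cluster-level t test figures of about 27% or 55%.

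This takes a confirmed or corrected figure and a few sentences. Enrolment does not change. The cost is that the stated power will be lower, under either alpha.
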